**Table 1. Overview of Testing Equipment Used in the Study**

| **General Name (Tentative Name for Unreleased Products)**  **Abbreviation, etc.** | **Model No. (Approval No.)** | **Unapproved** | **National Health Insurance Listing** | **Manufacturer** |
| --- | --- | --- | --- | --- |
| CO_2_ module 36552000 (capnography sensor) | CO_2_ sensor kit  (21400BZZ00536000) | No | No | Nihon Kohden  Corporation |
| CO_2_ module 36552000 *Attachment (ETCO_2_ nasal adaptor) | Nasal adaptor *Attachment for the CO_2_ sensor kit above. | No | No | Nihon Kohden  Corporation |
| Nasal pressure sensor cable | Resp-NP sensor | Yes | No | Nihon Kohden  Corporation |
| Resp-NP cannula | YH series respiratory test sensor cannula (14B2X10004TR0007). | No | Yes | Nissei Eco  Co., Ltd. |
| Multi-item monitor with major parameters 33586003 (monitor) | CSM-1000 Series Bedside Monitor Lifescope G *Including CSM-1901 (22500BZX00483000) | Partial  Unapproved | No | Nihon Kohden  Corporation |

1. **Examination/Testing/Evaluation Items, Methods and Schedule**
   1. **Schedule and Procedure**

The examination, testing and evaluation schedule will be as shown in the table below. The principal investigator or assistant investigators will carry out examination and testing, etc., in accordance with the schedule.

| Timing  Items | Screening  Test | During Treatment | End of  Treatment | After Treatment | | | | Following Day/  When Discontinued _g_ |
| --- | --- | --- | --- | --- | --- | --- | --- | --- |
|  |  |  |  | 30 min | 1 hr | 2 hrs | 3 hrs |  |
| Permissible range (days) | -7 | 0 |  |  |  |  |  |  |
| Consent obtained | ● |  |  |  |  |  |  |  |
| Patient background | ● |  |  |  |  |  |  |  |
| Subjective symptoms | ● | ● | ● | ● | ● | ● | ● | ● |
| Vital signs | ● | ● | ● | ● | ● | ● | ● | ● |
| Monitor (CSM-1901) recording |  | ●a |  | ●a | ●a | ●a | ●a |  |
| ECG monitor abnormality |  | ● |  |  |  |  |  |  |
| Height, weight and neck circumference | ● |  |  |  |  |  |  |  |
| ECOG-PS | ● |  |  |  |  |  |  |  |
| ASA classification | ● |  |  |  |  |  |  |  |
| Sleep apnea-related items | ● |  |  |  |  |  |  |  |
| 12-lead ECG | ● |  |  |  |  |  |  |  |
| Chest X-ray | ● |  |  |  |  |  |  |  |
| Ramsay sedation scale |  | ● | ● | ● | ● | ● | ● |  |
| Oxygen desaturation (<90%)  frequency and duration |  | ●b |  | ●b | | | |  |
| Oxygen desaturation (<95%) frequency |  | ●b |  | ●b | | | |  |
| Apnea (≥20 sec) frequency |  | ●b |  | ●b | | | |  |
| Oxygen desaturation (<90%)  oxygen desaturation (<90%) |  | ●b |  | ●b | | | |  |
| Oxygen desaturation (<95%)  oxygen desaturation (<95%) |  | ●b |  | ●b | | | |  |
| False alarm frequency |  | ●c |  | ●c | | | |  |
| Response to respiratory abnormality |  | ● |  |  |  |  |  |  |
| Technical trouble frequency |  | ●d |  |  |  |  |  |  |
| Position change frequency |  | ●d |  |  |  |  |  |  |
| BIS |  | ● |  |  |  |  |  |  |
| Sedative dose |  |  | ● |  |  |  |  |  |
| Coordination during treatment |  |  | ●e |  |  |  |  |  |
| Satisfaction with drug therapy |  |  |  |  |  |  |  | ●e |
| Support therapy |  | ● |  | ● | ● | ● | ● | ● |
| Observation of adverse events |  | ●f | ●f | ●f | ●f | ●f | ●f | ●f |

In some cases, data acquired prior to obtaining consent may be included in the study data. X-ray images and ECG data shall be acquired no more than 60 days prior to obtaining the consent of patients, and when no apparent heart disease or lung disease is observed, the use of such data is permitted and requires no retesting.

a: During treatment in the Safety Evaluation (Phase II), blood pressure, heart rate, SpO2, BIS and capnography/nasal pressure waveforms will be continuously recorded, while the doctor in charge of sedation monitors all items other than capnography waveforms. During the procedure that undergoes Usefulness Evaluation (Phase III), only one of capnography or nasal pressure will be recorded and displayed. After returning to the ward, SpO2 and capnography/nasal pressure waveforms (the same as those recorded during treatment) will be continuously recorded for a further three hours (one hour in the case of the usefulness evaluation).

b: During treatment the screens will be monitored and the state of respiration when SpO2 drops below 90% (frequency) and 95% (frequency) and oxygen desaturation (<90% and <95%) occurs will be recorded. In addition to the above, assistant investigators will analyze monitor records after the completion of the monitoring period and record the state of respiration when SpO_2_ drops below 90% (frequency and duration) and 95% (frequency), when oxygen saturation (<90% and <95%) occurs, and the frequency with which the patient experiences apnea (≥20 sec). Analysis of monitor records will be carried out for three hours after the completion of treatment for the Safety Evaluation (Phase II), and for one hour after the completion of the treatment for the Usefulness Evaluation (Phase III). (In the Safety Evaluation (Phase II), if respiratory abnormalities occur frequently after one hour has passed following the completion of the treatment, the duration of the observation period after the completion of the treatment for the usefulness evaluation will be reconsidered.)

c: In the post-treatment monitor analysis by the assistant investigators, if oxygen desaturation was not observed even without respiratory waveforms of more than three minutes, this will still be deemed to be a false alarm.

d: If technical trouble occurs, such as apnea or a respiratory abnormality being displayed due to a dislodged sensor, or if bodily movement occurs that requires two or more people to secure the safety of the patient or to continue the procedure, the doctor in charge of sedation will record such matters.

e: Operators will evaluate coordination during the treatment using VAS after the treatment has been completed. After confirming that the patient is fully awake after the treatment, on the same day, the degree of patient satisfaction regarding the treatment will be evaluated using VAS.

f: All events that occurred from the time of the commencement of the treatment will be checked to see if they equate to adverse events. All adverse events that occurred during the treatment period will be followed up during the post-treatment observation period. For details please see “8. Handling Adverse Events.”

g: If the study is discontinued, data that was scheduled to be obtained on the day following treatment will be collected, and no data will be collected after that using the testing equipment.

- - 1. Screening

The screening process will commence after consent has been obtained. The principal investigator or assistant investigators will carry out the following screening tests and select patients who satisfy the eligibility criteria and are not in conflict with the exclusion criteria. Items to check are shown below.

1. Patient background: sex, age, allergies, name of illness to be treated, history of illness, current medication, existing conditions, alcohol consumption, and history of smoking
2. Subjective symptoms
3. Vital signs: heart rate, blood pressure, temperature and SpO_2_
4. Height, weight and neck circumference

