| After entering the treatment room for invasive endoscopy | For the Safety Evaluation (Phase II), patients will be fitted with both a capnography monitor and a nasal pressure monitor. After the nasal pressure monitor is fitted, do not turn on the capnography monitor, only check the display of the nasal pressure monitor, and administer sedatives. The capnography waveforms will be recorded and used later for waveform analysis along with those from the nasal pressure monitor.  Propofol and fentanyl will be used as sedatives, and will be administered by an endoscopist who has been fully trained in sedation by an anesthesiologist. The strength of the sedatives during the procedure will be controlled between BIS 60 and 80 as shown on the monitor in both groups. Prior to the administration of sedatives, oxygen will be administered through a transnasal catheter at a rate of 2 l/min. Local pharyngeal anesthesia (8% lidocaine spray) will be sufficiently administered until the vomiting reflex disappears. Propofol and fentanyl will be administered in accordance with a predetermined protocol (see below), while monitoring the patient’s sedation depth and suitably adjusting the dose of each drug. Administration will be stopped when the procedure has been completed, and if respiration rate drops to ≤8 bpm, naloxone will be administered. Patient response will be verified by calling out to the patient, and after checking that there are no cardiorespiratory dynamic problems, the patient will be allowed to leave the treatment room.  In cases where SpO_2_ is observed to have declined (<90), apnea lasts for ≥20 seconds, or a respiratory abnormality (≤8 bpm or abnormal waveform) accompanied by a decline in SpO_2_ (<95%) is observed during sedation, the doctor in change of sedation will report the respiratory abnormality to the endoscopy team, and measures will be taken to improve respiration (see 5.7). When such measures have been taken, details regarding the respiratory abnormality that caused them are recorded in the check sheet.  Monitoring data will be analyzed for up to three hours after the treatment in the Safety Evaluation (Phase II). Later, assistant investigators will analyze the monitor waveforms. |

● Usefulness Evaluation (Phase III)

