| Before entering the treatment room for invasive endoscopy | Patients who undergo invasive endoscopy will be assigned to either the nasal pressure monitor group or the capnography group and single-blinded by going through the following steps.   1. A signed consent form will be obtained from each participant, their eligibility verified, and participants registered. 2. Assignment results will be sent from the registration center to the principal investigator or assistant investigators. |
| --- | --- |
| After entering the treatment room for invasive endoscopy | In the Usefulness Evaluation (Phase III), both the capnography group and the nasal pressure monitor group will be sedated using one type of monitor, which will be the one used in the group to which they were assigned.  The method of sedation and response used in cases of respiratory abnormality are the same as those used in the Safety Evaluation (Phase II) (see 5.6).  In the usefulness evaluation, monitoring data will be analyzed for up to one hour after treatment. Later, assistant investigators will analyze the monitor waveforms. |

- 1. **Response to Respiratory Abnormalities**

In cases where SpO_2_ is observed to have declined (<90), apnea lasts for ≥20 seconds or a respiratory abnormality (≤8 bpm or abnormal waveform) accompanied by a decline in SpO_2_ (<95%) is observed during sedation, the doctor in change of sedation will report the respiratory abnormality to the endoscopy team, and measures will be taken to improve respiration (see 5.7).

When SpO_2_ drops to below 90%, oxygen will be increased, the patient will be stimulated (call their name), airway management will be carried out (head tilt, chin lift, or postural change), and propofol and fentanyl administration will be stopped or adjusted as required. In cases where such procedures do not improve the situation, a nasal airway tube will be inserted or the endoscope will be removed and artificial ventilation provided using an Ambu bag (a bag valve mask).

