Testing equipment (novel nasal pressure monitor, general name: Multi-parameter Multi-function Monitor 33586003) has been developed by Nihon Kohden Corporation and the Department of Anesthesiology, Pain and Palliative Care Medicine of Chiba University Hospital based on their joint research. The nasal pressure monitoring sensor and the software for reading the sensor, which are connected to the patient monitor, are not approved as medical devices, but the patient monitor connected to them that displays the waveform has been approved (see the table below). The technology employed in this respiration monitoring system is the nasal pressure monitoring method that is actually used in nocturnal polysomnography. Changes in nasal pressure detected through a nasal cannula are measured with this equipment, and the fluctuations in pressure are converted to create respiratory waveforms for each patient.

- 1. **Storage of Testing Equipment**

The equipment to be tested (novel nasal pressure monitor), ETCO_2_ sensor and the nasal pressure sensor cable will be safely kept in accordance with the attached Testing Equipment Management Procedures.

- 1. **Important Findings regarding the Testing Equipment**
     1. **Capnography (ETCO_2_) Sensor and Nasal Adaptor**

There are no known reports of defects in ETCO_2_ sensors or adaptors that may cause adverse events. However, when using the equipment it is important to bear in mind the following:

• For patients with low ventilation volume, when the volume of respiratory dead space increases over ventilation volume, proper ventilation may not occur. In some cases, CO_2_ may enter the dead space and cause inaccurate measurements or make the detection of apnea difficult.

• When a patient is administered a volatile anesthetic drug during anesthesia, measurement errors may occur.

• For patients who are fitted with a nasal tube, take care when fitting the sensor not to put pressure on or dislodge the nasal tube.

* Reference: CO_2_ Sensor Kit TG-900 Series package insert.

- - 1. Nasal Sensor Cable and Resp-NP Cannula

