**Secondary Endpoints for Safety**

Adverse Event Occurrence Rate

NCI-Common Terminology Criteria for Adverse Events v4.0 (CTCAE Ver. 4.0) JCOG version will be used to evaluate adverse events.

Basis for Secondary Endpoint Selection for Usefulness

Items where a difference in occurrence frequency between the capnography group and the nasal pressure monitor group is considered to be important will be evaluated as secondary endpoints.

Basis for Secondary Endpoint Selection for Safety

General evaluation standards will be used.

- 1. **Exploratory Endpoints**
- Comparison with capnography waveforms.
- Waveform analysis at the time of respiratory abnormality.
- Consideration of respiratory abnormality-related risk factors (including obesity, age, history of smoking, drug administration dose, treatment duration, and SAS).

Basis for Exploratory Endpoint Selection

There is a possibility that nasal pressure monitoring can detect the minute changes in waveforms that appear prior to the appearance of a respiratory abnormality. We will compare the changes in the waveforms prior to any drop in SpO_2_ between the capnography group and the nasal pressure monitor group, and analyze to what degree the monitor observer is able to detect changes in waveforms. As there is also a possibility that nasal pressure monitoring can accurately detect the patterns for respiratory depression and obstructive ventilatory impairment, we will analyze the frequency of those events in both groups. We will also consider the relationship between respiratory abnormalities (hypoxemia, apnea and obstructive ventilatory impairment) and obesity, age, drug dose, procedure duration and SAS in order to identify factors relating to respiratory abnormalities.

1. **Statistical Considerations**

The statistical analysis plan overview for the clinical study is shown below. Statistical analysis plan details are contained in the Statistical Analysis Plan. Although the overview of the Study Protocol for the clinical study may be revised in the Statistical Analysis Plan, in cases where the primary endpoint definition or analysis method is to be changed, the Study Protocol will be revised.

- 1. **Analysis Population**
     1. **Full Analysis Set (FAS)**

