Frequency of apnea (≥20 sec), degree of patients’ satisfaction and coordination during procedure will be evaluated with capnography group and nasal pressure monitor group, and the difference between those two groups will be analyzed using Pearson’s chi-square test. Significance level will be 0.05 on both sides, and confidence interval, and **two-sided 95% confidence interval will be computed.**

- - 1. **Safety Analysis**

Frequency of adverse event occurrence is the evaluation items to consider safety, therefore data table will be created. To estimate the proportion, exact 95% confidence interval for binomial distribution will computed for each group. Inter-group comparison will be carried out as required using Fisher's exact test.

- - 1. **Intermediate Analysis**

Data will be locked when registration of all cases for the Safety Evaluation (Phase II) is completed. The fixed analysis results will be disclosed to the independent data-monitoring committee (IDMC) (see 11.6) that oversees the study. The IDMC will evaluate the fixed data, and when they find the following situation, the study will be discontinued without carrying out registration for the usefulness evaluation.

- Rate of discontinued cases due to default accounted for 20% or more.
- Hypoxemia (SpO_2_<90%) was found in 60% or more of the cases.
- The IDMC determined that it will be inappropriate to conduct usefulness evaluation.

When the IDMC verified the safety, the participants will be registered for the usefulness evaluation. No intermediate analysis will be carried out in the usefulness evaluation.

- 1. **Independent Data-Monitoring Committee (IDMC)**

The independent data-monitoring committee (IDMC) will be established for this study. The IDMC will be independent of the people who conduct the study, and consist of two or more specialists whose position have no conflict of interest with this particular clinical study. The IDMC will provide appropriate advice and guidance in order to secure the safety of the participants and ethical and scientific soundness, based on the data monitoring protocol that is determined elsewhere for the purpose of securing safety of the participants. In cases where serious adverse events appear in this clinical study, the principal investigator may request the IDMC to deliberate concerning whether or not the study should be continued or revision of the Study Protocol. The IDMC will serve in writing the results of the deliberation to the principal investigator.

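### In Phase III apnea is read from a different device in each arm, so the between-arm apnea test in 11.5.2.2 mixes true apnea with device detection

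*Protocol*

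**What the plan says.** Under Protocol 5.6, both Phase III groups "will be sedated using one type of monitor, which will be the one used in the group to which they were assigned". Footnote a to the schedule in 7.1 adds that "only one of capnography or nasal pressure will be recorded and displayed" during the procedure. On the ward, "SpO2 and capnography/nasal pressure waveforms (the same as those recorded during treatment) will be continuously recorded", for one hour in Phase III. Footnote b gives the source of the apnea count: assistant investigators go through the monitor records afterwards and note "the frequency with which the patient experiences apnea (≥20 sec").

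Apnea is a secondary usefulness endpoint (10.2). The stated basis for these endpoints is "Items where a difference in occurrence frequency between the capnography group and the nasal pressure monitor group is considered to be important". Section 11.5.2.2 says that apnea, satisfaction and coordination "will be evaluated with capnography group and nasal pressure monitor group", with the difference tested by Pearson's chi-square at two-sided 0.05 and a 95% confidence interval.

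The protocol also describes how the devices differ. Section 6.3.1 warns that in patients with low ventilation volume, dead space may in some cases "cause inaccurate measurements or make the detection of apnea difficult" for capnography. The Introduction reports that capnography is less reliable when CO2 is used and gives false alarms when the sensor is displaced. It lists insensitivity to the CO2 supply as a merit of nasal pressure. Only in Phase II is it planned that "patients will be fitted with both a capnography monitor and a nasal pressure monitor", with both waveforms stored.

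**The concern.** The randomised device is also the instrument that measures the outcome. If the two devices miss, or falsely show, 20-second apneas at different rates, the recorded proportions will differ even when patients in both arms stop breathing equally often. A true difference can also be hidden. Section 11.5.2.2 makes no allowance for this: it treats the two counts as the same quantity. At stake is what the trial may say about apnea, an endpoint chosen because a between-group difference is thought important. The statistical analysis plan could not repair this by modelling, because the second signal is never recorded in Phase III.

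**Working it through.** **Is there a common apnea measure in both arms?** None is specified. The vital signs listed during treatment (7.1.2.1) are blood pressure, mean blood pressure and heart rate. Respiration rate is listed only at the end of treatment and at the fixed times afterwards, which cannot count 20-second pauses. The count therefore rests on the assigned waveform.

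**The plan's own figure.** The protocol gives no figure for apnea. The Phase III size, set by hypoxemia, reproduces: 2 × 0.20 × 0.80 × (1.960 + 0.842)² / 0.15² = 111.6, so 112 per arm and 224 in total.

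**Effect of unequal detection.** Let π be the true proportion of patients with apnea, equal in both arms, *s* the proportion of such patients whom the device flags, and *f* the proportion of apnea-free patients whom it flags falsely. The recorded proportion is π*s* + (1 − π)*f*. The rejection probability of the uncorrected chi-square test (two-sided 0.05, 112 per arm) was obtained by enumerating the two binomials. The protocol gives none of π, *s* and *f*, so all values below are assumptions. The test is taken to compare patients with at least one recorded apnea. The value named first belongs to the device assumed to be the more sensitive.

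| π | *s* | *f* | Recorded | Rejects |
|---|---|---|---|---|
| 50% | 95% v 95% | 0 v 0 | 47.5% v 47.5% | 5% |
| 50% | 95% v 90% | 0 v 0 | 47.5% v 45.0% | 7% |
| 50% | 95% v 85% | 0 v 0 | 47.5% v 42.5% | 12% |
| 50% | 95% v 75% | 0 v 0 | 47.5% v 37.5% | 33% |
| 50% | 95% v 60% | 0 v 0 | 47.5% v 30.0% | 77% |
| 20% | 95% v 75% | 0 v 0 | 19.0% v 15.0% | 13% |
| 50% | 95% v 75% | 5% v 20% | 50.0% v 47.5% | 7% |
| 50% | 95% v 75% | 5% v 25% | 50.0% v 50.0% | 5% |
| 20% | 90% v 90% | 5% v 15% | 22.0% v 30.0% | 28% |

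For example, in the seventh row: 0.5 × 0.95 + 0.5 × 0.05 = 0.500 and 0.5 × 0.75 + 0.5 × 0.20 = 0.475. In the last row the device with more false positives records more apnea, the reverse of the rows with missed apneas only.

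**Masking.** Suppose apnea truly falls from 40% (capnography) to 27% (nasal pressure). With perfect detection the test rejects in 55% of trials. With assumed sensitivities of 60% and 90% the recorded rates are 0.40 × 0.60 = 24.0% and 0.27 × 0.90 = 24.3%, and it rejects in 5%.

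**The case against.** The strongest reply is that the size of the problem is unknown and may be small. With 95% v 90% detection the excess over 5% is slight, and false positives in the less sensitive device can cancel its misses. The figures also treat detection as per patient. If 95% v 75% applied to each event independently, a patient with two apneas would be flagged with probability 1 − 0.05² = 99.8% v 1 − 0.25² = 93.8%, and at a 50% true rate the test would reject in about 8% of trials. This stands as a limit on the size. It does not supply a common yardstick.

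The protocol also has partial safeguards. Footnote c treats more than three minutes without a waveform and without desaturation as a false alarm. Footnote d has apnea displayed through a dislodged sensor recorded as technical trouble. These cover part of the artefact from false apneas and none from missed ones. The warning in 6.3.1 is limited to low ventilation volume and to some cases, so it does not show that capnography generally misses apnea.

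A reader might infer that the better detector must look harmful and the poorer one protective. The documents do not support that direction, because the Introduction also cites capnography false alarms, which could add apneas to that arm. A reader might also carry the criticism over to the exploratory waveform comparison in 10.3. Part of the stated aim there is to learn what the devices and their observers can detect, so detector performance is partly the intended object.

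**Conclusion.** The point holds as a fault in a secondary analysis. Followed exactly, the plan tests a mixture of true apnea and device detection, and nothing recorded in Phase III can separate the two. That conclusion needs no assumed number. The size does: with no true difference, the assumed values above give rejection between about 5% and 77% for a nominal 5% test. The upper figures need large sensitivity gaps that the protocol neither states nor excludes.

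It would go too far to say that the test measures only the detectors, or that the result cannot be interpreted at all. True apnea still contributes, and each arm's count can be read as device-detected apnea. Nor does the fault reach the primary endpoint: SpO2 below 90% is measured alike in both arms. Section 11.5.2.2 itself places the secondary analyses in a supplementary role.

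**What to change.** In 11.5.2.2, remove the between-arm significance test for apnea. Report apnea within each arm as device-detected apnea with a 95% confidence interval, and state that the two counts are not comparable as patient apnea. Name the endpoint the same way in 10.2. The paired Phase II recordings can be used to estimate agreement between the devices, which would help readers judge the Phase III counts. The cost is an amendment of wording and the loss of one formal secondary comparison.

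Optional, if the sponsor accepts a second sensor in Phase III: record both signals, display only the assigned one, and count apnea in both arms from the same stored signal with the arm hidden from the reader. This would give a common yardstick, but the signal would still come from one of the two devices under comparison, and staff would still respond to a different display in each arm. It also adds a nasal sensor for every Phase III patient, so it is not needed to resolve the point.
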